### 2.6. Study Interventions

The *L. plantarum* P9 and placebo powders will be manufactured in parallel and independently by Research and Development Department, Jiangzhong Pharmaceutical Company Limited (Nanchang, China). Briefly, the preparation procedure consists of three steps: weighing, mixing, and packaging. *L. plantarum* P9 powder is composed of 20% maltodextrin, 20% orange powder, 20% maltitol, and 40% *L. plantarum* P9, while placebo powder consists of 60% maltodextrin, 20% orange powder, and 20% maltitol. Raw materials for *L. plantarum* P9 and placebo powders are mixed using a Hopper mixer (hit-400) and sealed into 2 g packages. The temperature is controlled at 25 ± 2°C, and the relative humidity is less than 65% during the three steps. In the study, when the product of *L. plantarum* P9 powder is manufactured, a randomized sample is sent to Jinhua Yinhe Biotechnology Co., Ltd. (https://yinhewdy168.foodmate.net/) for quality inspection. The activity of probiotics is greater than 67 billion colony-forming units (CFUs)/g.

The study will include three phases (Table 1), including a screening period (an observation period prior to treatment administration), an observation period during administration, and an observation period after administration. The interventions in each phase will be administered as follows:Period of screening (preadministration observation period) (days 14 to 0): in this phase, volunteers will not receive the intended interventions, i.e., probiotics and placebo. Eligibility screening will be performed as described during volunteer recruitment (Table 1).Observation period during administration (days 0 to 28): (1) Probiotics group: volunteers will take 1 package of *L. plantarum* P9 powder directly or with warm water (below 40°C) on a full stomach at a dose of 100 billion CFUs per day; if antibiotics must be taken, probiotics should be taken 2 hours later. (2) Placebo group: volunteers will take the placebo in the same manner as the probiotics group. The placebo contains no probiotics but has the same appearance, packaging, and taste as the *L. plantarum* P9 powder.All remaining probiotics or placebo (unused) and empty (used) packages will be collected at the end of this period to monitor compliance. During the study, both probiotics and placebo will be stored in a cool, dry place away from direct sunlight.Postadministration observation period (days 29 to 42): no probiotics or placebo will be taken.

### 2.7. Prohibited Confounding Interventions

The following treatments are prohibited during the study: (1) probiotics, prebiotics, and foods containing probiotics (such as yoghurt) other than the *Lactobacillus plantarum* used in this study; (2) antianxiety, antidepressants, and other psychotropic drugs; and (3) other substances designed to improve intestinal symptoms.

In addition, antibiotics will be monitored during the study, and normal dietary habits will be recommended. All concomitantly used substances/drugs related to defecation should be recorded daily in the online defecation diary (Figure 2), and explanations are needed.

### 2.8. Primary Outcome

A defecation diary developed with reference to the literature [32, 53–56] will be completed daily online by the participants (Figure 2). Based on the diary, the changes in primary and some of the secondary outcomes from day 0 (week 0) to day 42 (week 6) will be evaluated.The primary outcome measure is the weekly mean frequency of complete spontaneous bowel movements (CSBMs) [32, 54, 55].

A CSBM is defined as the ability to achieve a complete bowel movement without the use of any drugs or other auxiliary measures during the previous 24 hours. Based on the diary (Figure 2), the weekly mean frequency of CSBMs from day 0 (week 0) to day 14 (week 2), day 28 (week 4), and day 42 (week 6) will be evaluated [32, 54, 55] (Table 1).

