### 2.12. Sample Size

This study is a clinical trial during which volunteers will consume a sample medication or placebo for 28 days and will be followed up for 42 days. The primary outcome measure is the weekly frequency of CSBMs. The expected weekly frequencies of CSBMs on day 28 are 1.1 in the control group and 4.1 in the probiotic group, with a between-group difference of 3. Given a standard deviation *S* = 6, *α* = 0.05, and *β* = 0.20, the sample size should be at least 63 volunteers per group, as calculated with the formula for statistically significant effectiveness. After considering the drop-out rate (20% or lower), the sample size should be 76 or more participants per group. The final sample size will be 100 participants per group for a total of 200 volunteers.

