### 2.15. Statistical Analysis

The intention-to-treat (ITT) analysis will be conducted between the two groups. Then, the following four data sets will be used for the per-protocol (PP) analysis: (1) the data from all participants who completed the follow-up and (2) a subgroup analysis regarding levels of compliance (≥80%, 60–80%, and <60%) to validate the robustness of the results. The hypothesis will be tested using the methods described below during the ITT and PP analyses.

First, the Wilcoxon signed-rank sum test will be used for the outcome measures, including the weekly mean frequency of CSBMs, weekly mean stool appearance score, weekly mean difficulty of passing stool score, weekly mean frequency of SBMs, QOL score, and emotional status score, at each observation point to analyse the intergroup differences in each outcome measure. The chi-square (*χ*^2^) test will be used for the outcome measures, namely, the percentage of volunteers with a weekly mean frequency of CSBMs ≥3 and WPUAMA, at each observation point. In the analyses, the *P* value indicating statistical significance will be set to 0.05.

Then, the Kruskal–Wallis rank sum test will be used for multiple comparisons of outcome measures, including the weekly mean frequency of CSBMs, weekly mean stool appearance score, weekly mean difficulty of passing stool score, weekly mean frequency of SBMs, QOL score, and emotional status score, and the *χ*^2^ test will be used for multiple comparisons of outcome measures, including percentage of volunteers with a weekly mean frequency of CSBMs ≥3 and WPUAMA, at each observation point to identify the intragroup changing trends in consecutive phases, namely, pre-, during, and postprobiotic administration. In the analyses, the *P* value indicating statistical significance will be adjusted to 0.05/[*k* (*k* −1)/2], where *k* is the number of sample groups included in the comparison.

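### Sections 2.8 and 2.15 name no decisive time point for the primary outcome and test it at days 14, 28 and 42, each at unadjusted 0.05, while the trial is sized on one test at day 28

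*Protocol article*

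**What the plan says.** Section 2.8 gives the measure without a day: "The primary outcome measure is the weekly mean frequency of complete spontaneous bowel movements (CSBMs"). It then lists the evaluation as "weekly mean frequency of CSBMs from day 0 (week 0) to day 14 (week 2), day 28 (week 4), and day 42". Table 1 ticks this outcome at days 0, 14, 28 and 42 and gives none of them a special status.

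Section 2.15 applies the between-arm test "at each observation point to analyse the intergroup differences in each outcome measure", and for these analyses the P "value indicating statistical significance will be set to 0.05". The next paragraph of 2.15 turns to comparisons within each arm, "to identify the intragroup changing trends in consecutive phases". Only there is the threshold lowered: the P "value indicating statistical significance will be adjusted to 0.05" divided by the number of pairwise comparisons, k(k − 1)/2.

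Section 2.12 is the one place where a single day appears: "The expected weekly frequencies of CSBMs on day 28 are 1.1 in the control group and 4.1 in the probiotic group". With a standard deviation of 6, α = 0.05 and β = 0.20 it arrives at 63 per group.

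**The concern.** Sections 2.8 and 2.15 put three post-baseline comparisons of the primary outcome on an equal footing, each at the full 0.05. No hierarchy, gatekeeping or success rule is stated. The sample size assumes one comparison at one day, so the design calculation and the analysis section describe different trials.

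The three days also answer different questions. Day 14 is mid-treatment and day 28 is the end of administration. Day 42 follows two weeks without product (section 2.6), so it speaks to persistence. If only day 14 or only day 42 were significant, the present text would not stop that result from being reported as success on the primary outcome, at a time point the trial was not sized for and with more than a 5% chance of a false positive.

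The plan does recognise multiplicity elsewhere. It adjusts the within-arm comparisons in 2.15 and applies a Benjamini–Hochberg correction to the metagenomic and metabolomic data. The randomised comparison of the primary outcome is left without an adjustment.

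**Working it through.** **Inputs from the protocol.** Difference 4.1 − 1.1 = 3, SD 6, α = 0.05, β = 0.20, 63 per group before dropout, 100 per group final (2.12). Post-baseline evaluations at days 14, 28 and 42 (2.8, Table 1). Level 0.05 per between-arm test (2.15).

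**Inputs assumed.** The protocol gives no correlation between visits, so a range from 0 to 0.9 is shown. It does not state whether the tests are one- or two-sided; step 1 settles this for the sample size. The test statistics are treated as jointly normal.

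**Step 1: reproduce the plan's figure.**
n per group = 2(z₀.₉₇₅ + z₀.₈₀)² SD²/Δ² = 2 × (1.960 + 0.842)² × 36/9 = 62.8, rounded up to 63. This matches the plan. A one-sided calculation would give 50. The stated 63 therefore belongs to one two-sided test at 0.05.

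**Step 2: family-wise error over three tests.** The quantity is the probability that at least one |Z| exceeds 1.96 when there is no effect at any day.

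Independent tests: 1 − 0.95³ = 0.143.

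Correlated tests, by simulation of three standard normal statistics (2,000,000 draws):

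| Assumed correlation | Equal between all visits | Decaying with distance, AR(1) |
|---|---|---|
| 0 | 14.3% | – |
| 0.3 | 13.6% | – |
| 0.5 | 12.5% | 12.9% |
| 0.7 | 10.9% | 11.4% |
| 0.8 | 9.8% | 10.3% |
| 0.9 | 8.3% | – |

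Counting only false findings in favour of the probiotic, the same simulation gives 7.3% at correlation 0, 4.9% at 0.8 and 4.2% at 0.9 (equal correlation), against a nominal 2.5%.

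**Step 3: what each remedy costs** (normal approximation).
- Day 28 as the single test: power = Φ(3/(6√(2/n)) − 1.96). At n = 100 this is Φ(3.536 − 1.960) = 94%; at 80 completers it is Φ(3.162 − 1.960) = 89%.
- All three days kept, at 0.05/3 = 0.0167 each: 84 evaluable per group for 80% power per test, or 84/0.8 = 105 after 20% dropout. Power per test is about 87% at 100 per group and about 78% at 80 completers.

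**The case against.** The strongest reply is that day 28 is already implied. Section 2.12 restates the primary outcome and then gives the expected values for day 28, with a single α. Day 28 is also the last day of administration. On that reading days 14 and 42 merely describe onset and persistence, and the error rate is 5%. This is a sensible reading and it points to the right repair. But 2.12 is a planning assumption: it does not call day 28 the primary time point, and 2.8, 2.15 and Table 1 do not take it up.

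A second reply is that the plan contains no rule that one significant day suffices. That stands. A reader might infer that the trial's false-positive rate simply is 10% to 14%. The documents do not support that. The inflation depends on a success rule that the plan neither states nor excludes. If all three days had to be significant, the error would be below 5%. The range also depends on a correlation that is not given. The 14% end needs independent visits, which is unlikely for diary counts from the same people two weeks apart, and at 0.9 the figure is about 8%.

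A reader might also count day 0 as a fourth test because Table 1 ticks it. A difference before treatment is not an efficacy claim, so it does not belong in this error rate.

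A third reply is that time point and hierarchy are matters for a statistical analysis plan that is not shown. This holds only in part. The article itself fixes 0.05 for the between-arm tests and confines the adjustment to the within-arm ones, so the rule is stated here and not merely deferred.

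**Conclusion.** The point holds as a mismatch between sections, with a conditional consequence. Sections 2.8 and 2.15 leave the deciding day open and test three post-baseline days at full 0.05; section 2.12 sizes the trial for one test at day 28.

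If any one of the three could be claimed as success, the two-sided family-wise error is about 8% to 14%, for assumed between-visit correlations from 0.9 down to 0. If day 28 alone decides, the error is 5% and the sample size is consistent with the analysis. The text should say which applies.

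**What to change.** State in 2.8 and 2.15 that the between-arm difference in weekly mean CSBMs at day 28 is the single confirmatory test, two-sided at 0.05. Make days 14 and 42 secondary: either test them in a fixed sequence after day 28, in an order written down beforehand, or report them with confidence intervals only. Describe day 0 as baseline, not as an efficacy comparison.

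The change is one of wording and should be made before the randomization sequence is opened for any interim or final analysis. The 63 per group and the power at day 28 stay as they are. The price is that a result at day 14 only or day 42 only cannot be claimed as primary success.

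If the sponsor wants all three days to be able to carry the claim, a Bonferroni level of 0.0167 is also valid, but at 80 completers per group it lowers power per test from about 89% to about 78%.

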### 2.9. Secondary Outcomes

Based on the diary (Figure 2), the changes in the percentage of volunteers with a weekly mean frequency of CSBMs ≥3 [32, 54, 55], changes in the weekly mean frequency of spontaneous bowl movements (SBMs) [32, 54–56], weekly mean stool appearance score [53], weekly mean difficulty of passing stool score, and weekly percentage of volunteers who use auxiliary measures to assist with defecation (WPUAMA) will be evaluated each week from day 0 (week 0) to day 14 (week 2), day 28 (week 4), and day 42 (week 6). An SBM is defined as a bowel movement achieved without the use of any drugs or other auxiliary measures during the previous 24 hours [32, 54, 55] (Table 1).The Patient Assessment of Constipation Quality-of-Life (PAC-QOL) questionnaire (Appendix 5 [56, 57]) will be used to evaluate the QOL score on days 0, 14, 28, and 42.The Depression, Anxiety and Stress Questionnaire (DASS-21) [58, 59] (Appendix 6) will be completed online on days 0 (baseline), 14, 28, and 42 and used to assess the participants' emotional status (depression, anxiety, and stress) within the past week (Table 1).For the indicator of the gut microbiome, DNA will be extracted from the stool samples with the QIAamp Fast DNA Stool Mini Kit (Qiagen, Hilden, Germany) according to the manufacturer's instructions, and the quality of DNA will be examined using agarose gel electrophoresis and a NanoDrop spectrophotometer. Shotgun metagenomic sequencing will be performed on all samples using an Illumina HiSeq 2500 instrument. Libraries will be constructed from DNA fragments with a length of ∼300 bp; paired-end reads will be generated by sequencing 150 bp in the forward and reverse directions. Meanwhile, the metagenomic analysis will include several parts: the analysis of alpha diversity and beta diversity in each group to understand whether the differences in the microbiota compositions of groups are significant and a comparison of the taxonomic characteristics of the study group and the control group at the level of phylum, genus, and species to identify specific genes related to the individual differences of constipation. Metagenomic biological pathway analysis will be used to evaluate the effect of probiotics on the function of gut metagenomics in patients with constipation and to explore the metagenomic biological pathways contributing to the mechanism underlying the effect of probiotics on the treatment of constipation.For the indicator of the faecal metabolome, stool samples will be extracted using the protein precipitation method, and the supernatant will be transferred to sample vials for LC-MS/MS analysis. The original data will be subjected to peak alignment, retention time correction, and peak area extraction using the XCMS-Plus program. The structure of metabolites will be identified by accurate mass matching (<5 ppm) and two-level spectrum matching, and the METLIN database will be retrieved. We will then delete data with missing values > 50% in the group, normalize the data, and conduct multidimensional statistical analysis, including unsupervised principal component analysis (PCA), supervised partial least squares discriminant analysis (PLS-DA), and potential differentially abundant metabolite analysis. The metabolomic analysis might further identify the potential differentially abundant metabolites of probiotics in the treatment of constipation, and a correlation analysis between the gut microbiota and metabolites will be performed.

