### 2.2. Inclusion Criteria

Eligible patients should fully meet the Rome IV criteria [2]:(1)Onset of the following symptoms for at least 6 months before enrolment and symptoms within the past 3 months that meet the following criteria [2, 52]:Two or more of the following symptoms: (a.) difficulty passing stool, at least 25% of defecations; (b.) lumpy or hard stool, at least 25% of defecations (Bristol Stool Form Scale (BSFS) types 1 or 2 (Appendix 3) [53]); (c.) incomplete defecation in at least 25% of defecations; (d.) sense of anorectal obstruction in at least 25% of defecations; (e.) need for manual assistance for defecation (such as using fingers to assist with defecation or pelvic floor support) in at least 25% of defecations; and (f.) fewer than 3 spontaneous bowel movements (SBMs) per week.Loose stool rarely occurs without the use of laxatives.Insufficient stools are rarely present without the use of laxatives.(2)Willing to sign the informed consent form (Appendix 4)(3)The volunteers involved in this study will be patients with chronic constipation aged 18–65 years. For patients aged from 18 (exclusive) to 50 (inclusive) years, the result of stool tests (including occult blood) conducted during the screening period must be normal or abnormal but determined to be clinically irrelevant by the investigators. For patients aged 50 (exclusive) to 65 (inclusive) years, the result of a colonoscopy performed at a tertiary or higher-level hospital within the past 6 months must be normal or abnormal but determined clinically irrelevant by the investigators.

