### 2.4. Volunteer Recruitment

The investigators will recruit volunteers from the public through in-person communication, posters, and WeChat promotions. Volunteers can scan a WeChat two-dimensional (QR) code to register for enrolment, submit their personal information, and answer questions related to inclusion and exclusion criteria. Volunteers will undergo a procedure that includes three rounds of screening. First, the investigators will collect and collate the volunteers' registration information and, according to the information provided by registrants, invite potentially eligible candidates to participate in a central consultation with clinical specialists for further screening and selection of eligible volunteers. Second, during the central consultation, trained study implementers will introduce the trial to volunteers in the form of a video and information sheets describing the main aspects of the trial and discuss the information provided in the video and information sheets. Then, volunteers will meet with the clinical specialist to confirm their registration information, especially regarding inclusion and exclusion criteria. Third, volunteers will sign an informed consent form in the presence of a member of the data management team (DMT). Then, volunteers will undergo a 14-day screening period when they will not be allowed to take any medicines or health products to improve their constipation symptoms. Each volunteer will be asked to collect one stool sample and complete an online diary entry daily (Figure 2). At the end of the screening period, the diary and stool sample results will be reviewed and used to select eligible volunteers. Subsequent steps will include the formal intervention and follow-up visits (Figure 1).

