**Figure 2 fig2:**
[figure not shown]
Defecation diary.

**Table 1 tab1:** Study and follow-up schedule.

Item		Screening period (preadministration observation period)		Observation period during administration		Postadministration observation period
		Visit 0	Visit 1	Visit 2	Visit 3	Visit 4
		(Days −14 to −1)	Day 0	Day 14	Day 28	Day 42
Collection of volunteers' basic information	√					
Screening	√					
Signing informed consent form	√					
Stool test (including occult blood)	√					
Defecation diary	Completed online daily					
Primary outcomes	Weekly mean frequency of CSBMs		√	√	√	√

Secondary outcomes	Weekly mean frequency of CSBMs ≥3		√	√	√	√
	Weekly mean frequency of SBMs		√	√	√	√
	Weekly mean stool appearance score		√	√	√	√
	Weekly mean difficulty of passing stool score		√	√	√	√
	Weekly mean stool appearance score		√	√	√	√
	Weekly mean difficulty of passing stool score		√	√	√	√
	WPUAMA		√	√	√	√
	Quality-of-life score		√	√	√	√
	Emotional state score		√	√	√	√
	Gut microbiome		√		√	√
	Faecal metabolome		√		√	√

Safety measures	Adverse events (AEs)			√	√	√
	Serious adverse events (SAEs)			√	√	√

Verification of compliance with the intervention					√	
Concomitant medications			√	√	√	√

*Note*. Except for the quality-of-life score and emotional state score, the other outcome measures are calculated from the defecation diary.

**Table 2 tab2:** The comparisons of methodologies among the present and previous RCTs related to the effect of probiotics on chronic constipation.

Study	Design	Allocation concealment/Blinding/ITT analysis/Description of withdrawals or dropouts	Sample size (probiotics:control)	Population	Age (years)	Diagnostic criteria	Intervention	Comparator	Probiotic strain	Outcomes	Daily dosage (CFUs)	Study stage (duration)
Agrawal [68]	Randomized, double-blind, controlled, parallel group study	Yes/Yes/Yes/Yes	17/17	Irritable bowel syndrome with constipation in females	20–69	Rome III criteria for constipation predominant IBS	A fermented milk containing probiotics	A milk-based nonfermented dairy product	*Bifidobacterium lactis*	Abdominal distension, gastrointestinal transit, abdominal symptoms, and bowel habit	1.25 × 10^10^	Screening period/baseline (11 days), administration period (28 days), postadministration period (7 days)

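### The between-group chi-square for CSBMs ≥3 ignores each volunteer's day-0 status, a valid choice that gives up a modest amount of precision

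*Protocol article*

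**What the plan says.** Section 2.9 of the Protocol article lists first among the secondary outcomes "the changes in the percentage of volunteers with a weekly mean frequency of CSBMs ≥3", followed from day 0 to days 14, 28 and 42. It is a status at each visit. It requires neither a value below 3 at entry nor a rise from day 0.

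Section 2.15 fixes the between-group analysis: the chi-square "test will be used for the outcome measures, namely, the percentage of volunteers with a weekly mean frequency of CSBMs ≥3 and WPUAMA", applied at each observation point, with the significance level at 0.05. No covariate or stratum is named. Day 0 appears only as its own time point and in the within-group comparisons across phases.

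Section 2.2 admits volunteers with "Two or more of the following symptoms". Low frequency is one option of six, and it is worded as "fewer than 3 spontaneous bowel movements (SBMs) per week", so it counts SBMs and not CSBMs. Section 2.4 adds that "the diary and stool sample results will be reviewed and used to select eligible volunteers", without a CSBM threshold. Table 1 marks the diary as "Completed online daily" and assesses CSBMs ≥3 on day 0.

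**The concern.** A volunteer with hard stools and difficult passage in a quarter of defecations meets the symptom count while having three or more CSBMs a week. Such a volunteer is likely to be at ≥3 again on day 28 in either arm. This has two effects:

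- **Dilution.** The difference in percentages shrinks, because part of each arm is at ≥3 whatever it receives.
- **Noise.** Chance differences between volunteers who start above and below 3 enter the error term of an unadjusted test, although day-0 status would explain them.

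An analysis that uses day-0 status can remove the second effect but not the first. What is at stake is some power and a wider interval for this secondary outcome. The validity of the comparison is not at stake.

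**Working it through.** **The plan's own figure.** No rate or power is stated for CSBMs ≥3. The only sample-size figure concerns mean CSBMs (section 2.12): difference 3, SD 6, α = 0.05, β = 0.20. Two-sided, n = 2 × (1.960 + 0.842)² × 6²/3² = 62.8, so 63 per group, as stated. Of the planned 100 per group, the 20% dropout allowance leaves 100 × 0.80 = 80 evaluable.

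**Assumptions (not in the documents).** A share q of each arm is at ≥3 on day 0. Among those below 3 at entry, 20% (control) and 40% (probiotic) are at ≥3 on day 28. Of those at ≥3 at entry, 90% stay there in both arms.

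**Chi-square.** The percentages are pC = (1−q)×0.20 + q×0.90 and pT = (1−q)×0.40 + q×0.90, with mean p̄. Power = Φ{[(pT−pC) − 1.96√(2p̄(1−p̄)/n)] / √([pC(1−pC) + pT(1−pT)]/n)}.

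At q = 10%: pC = 0.27, pT = 0.45, p̄ = 0.36. The null standard error is √(2×0.36×0.64/80) = 0.0759 and the alternative one is √((0.1971+0.2475)/80) = 0.0745. Power = Φ[(0.18 − 0.1488)/0.0745] = Φ(0.42) = 66%.

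**Stratified by day-0 status.** The difference is the same, but the variances are those within strata. At q = 10% the null variance term is 0.9×0.30×0.70 + 0.1×0.90×0.10 = 0.198, so the standard error is √(2×0.198/80) = 0.0704. The alternative one is √((0.9×0.40 + 0.1×0.18)/80) = 0.0687. Power = Φ[(0.18 − 0.1379)/0.0687] = Φ(0.61) = 73%.

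Simulation gives the same picture (80 per arm; simulation error and rounding of about one point):

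| Share at ≥3 on day 0 | pC / pT | Chi-square power | Mantel-Haenszel power |
|---|---|---|---|
| 0% | 0.200 / 0.400 | 81% | 80% |
| 2% | 0.214 / 0.410 | 78% | 79% |
| 5% | 0.235 / 0.425 | 73% | 77% |
| 10% | 0.270 / 0.450 | 66% | 73% |

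At 0% the two tests are in effect the same. At 10% the chi-square loses about 15 points against 0%, and stratifying recovers about 7 of them. The rest is dilution: the difference has fallen from 0.20 to 0.18. Type I error was 4.6% to 5.3% for both tests.

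**How large can the share be?** Section 2.12 expects a control mean of 1.1 CSBMs a week on day 28. Every control at ≥3 contributes at least 3, so the mean is at least 3 × pC:

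- At 10%: 3 × 0.27 = 0.81, which is compatible.
- At 20%: pC = 0.8×0.20 + 0.2×0.90 = 0.34, floor 1.02. The other 66% of controls would have to average (1.10 − 1.02)/0.66 = 0.12 a week.
- At 30%: pC = 0.7×0.20 + 0.3×0.90 = 0.41, floor 1.23, above 1.1.

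**Continuous day-0 value.** A separate simulation used 100 per arm, 20% against 38% overall, shares of 5% to 10%, and a correlation of 0.3 to 0.7 between day 0 and day 28. Chi-square power was 0.80 to 0.81. Logistic regression on continuous day-0 CSBMs gave 0.83 to 0.93.

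**The case against.** The strongest reply is that this is a preference and not an error. The chi-square holds its level under randomisation, the outcome is secondary, and no power claim attaches to it. All of that stands. A reader might infer that volunteers already at ≥3 bias the comparison. They do not, because randomisation distributes them by chance and the simulated type I error is near 5%.

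The share at ≥3 on day 0 is also unknown. Volunteers must have symptomatic Rome IV constipation, and the screening diary may remove some with frequent CSBMs. The documents show that such volunteers can enter, not that many will. This stands too, and it is why the size is given as a range starting at zero.

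Other tempting readings go too far:

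- **A loss of 25 points or more.** This needs shares of about 20% or above, which under the assumed rates barely fit or contradict the planned control mean. That mean is a planning expectation, and lower retention would loosen the limit, but nothing in the documents points to such shares.
- **The diary would restore the lost power.** It restores about half at best in the scenarios with stratification, because dilution remains.
- **Volunteers at ≥3 cannot respond.** The outcome is a status. They count when still at ≥3 and do not count when they fall below.
- **The test contradicts an outcome worded as a change.** The change is in a group percentage. Comparing that percentage between arms at each visit, and testing trends within arms separately, is consistent with section 2.9.

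**Conclusion.** The point holds as a minor efficiency matter. Section 2.15 states an unadjusted test, so this is a choice made in the document and not a detail left open. It sets aside a baseline value that the trial already collects. Under the stated assumptions the gain from stratifying is nil if nobody enters at ≥3, about 1 to 2 points of power at a 2% share, about 4 at 5% and about 7 at 10%. The exact size cannot be fixed, because the documents give neither the day-0 share nor the response rates by day-0 status. Using the continuous day-0 frequency may gain more, depending on its correlation with later values. The planned comparison remains valid if left unchanged.

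**What to change.** For the between-group comparison of CSBMs ≥3 on days 14, 28 and 42, replace the plain chi-square by one of these, chosen before unblinding:

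- logistic regression on arm and continuous day-0 weekly CSBM frequency, reporting a standardised (marginal) risk difference with 95% CI, since the model's own coefficient is a conditional odds ratio; or
- a Mantel-Haenszel test and risk difference with 95% CI, stratified by day-0 status (≥3 or <3).

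Keep all randomised volunteers in the analysis and show the raw percentages by arm and visit as description. The same adjustment, by day-0 use of auxiliary measures, can be applied to WPUAMA; no gain was calculated for that outcome.

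The cost is one sentence in the analysis section and a few lines of code. No new data and no change to eligibility are needed.
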